**Figure 1 fig1:**
[figure not shown]
The process of the health communication campaign.

The study is scheduled to take place from March 2024 to October 2026 at 12 participating centres in seven research sites (Lahore, Karachi, Islamabad, Multan, Quetta, Hyderabad and Peshawar) in Pakistan.

### Phase 0: baseline assessment

2.2

The research team will recruit participants (*n* = 600) from seven project sites across Pakistan for a baseline assessment measuring existing indicators of knowledge, attitudes and practices on burn prevention, psychological variables, health information-seeking variables and demographics (see Table 1 for the full list of variables).

**Table 1 tab1:** Outcome measures collected at the data collection points throughout the study.

Outcome measures	Baseline (t0)	Time 1 (t1)	Time 2 (t2)
KAP ^1,2^	X	X	X
SSS-S^1^	X	X	X
GRAT^1^	X	X	X
MLQ^1^	X	X	X
WHS^1^	X	X	X
CPOS^1^	X	X	X
TSWLS^1^	X	X	X
COPE^1^	X	X	X
SLAS^1^	X	X	X
BRS^1^	X	X	X
Photo Reflection^1,2,3,4*^		X	X
Campaign effectiveness^1,2,3,4^			X

Survivors^1^; family members ^2^; health care professionals^3^; key informants^4^; the photo reflection workshops are for burn survivors only except for the workshops conducted at the end of the public exhibitions^*^; t0, baseline; t1, end of photo reflection workshop; t2, end of closed exhibitions; t3, end of closed exhibition; t4, end of the final public project exhibition; KAP, Knowledge Attitude and Practice Scale; MLQ, Meaning in Life Questionnaire; GRAT, Gratitude and Resentment Scale; WHS, Adult Workers Hope Scale; CPOS, Patient Optimism Scale; TSWLS, Temporal Satisfaction with Life Scale; COPE, COPE Inventory; SIAS, Social Interaction Anxiety Scale; SSS, Self-Stigma Scale; BRS, Brief Resiliency Scale.

Ethical approval was obtained from the Pakistan National Bioethics (Approval ID: NBC-985) and Manchester University Research Ethics Committees (Approval ID: 2023–18,027-31199).

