### Research design

2.1

This study is a cohort study with three measurement points conducted at 6- to 12-month intervals (*n* = 600). The impact of the health communication campaign will be evaluated by measuring indicators of knowledge, attitudes and practices related to burn first aid, as well as psychological variables and health information-seeking variables, among the following groups: the exposure group (i.e., burn survivors [*n* = 200] and caregivers [*n* = 100] exposed to campaign messages), the non-exposure group (i.e., burn survivors [*n* = 250] not exposed to campaign messages) and the Photovoice group (i.e., burn survivors [*n* = 50] who participate in Photovoice and are exposed to the campaign messages). Figure 1 presents the campaign process and the planned activities in different phases.

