#### Procedure

2.2.3

The research team will recruit burn survivors and caregivers from 12 burn centres based in seven project sites across Pakistan to measure existing indicators of knowledge, attitudes and practices on burn prevention, as well as psychological variables, health information-seeking variables and demographics.

Burn survivors and their family members will be invited to fill out online questionnaires (baseline assessment). The research assistants will distribute posters and leaflets at participating centres and waiting rooms, introducing the study and providing the research team’s contact information for further enquiries. The research assistants will also attend the patient and/or family consultations to introduce the study and obtain consent for a follow-up call with the research team. During the follow-up call (within the first 24 or 48 h after the initial contact), the research assistants will ensure that interested burn survivors and their family members understand what their participation entails, and will confirm their willingness to provide informed consent. After informed consent is obtained, burn survivors and their family members will be asked to complete the same questionnaires at 6- to 12-month intervals up to a total of two times throughout the study (see Figure 2 for the CONSORT diagram). If they are literate, as determined during the informed consent process, they will receive a text message with a Qualtrics questionnaire link. If they are illiterate, a research assistant from the research team will call them for the completion of the questionnaires on the phone. Consent for collecting personal information will be obtained during the informed consent process.

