##### Brief Resiliency Scale (BRS)

2.2.5.10

The BRS is a six-item self-report scale (47). Sample items include the following: ‘I tend to bounce back quickly after hard times’; ‘I have a hard time making it through stressful events’; ‘It does not take me long to recover from a stressful event’; and ‘It is hard for me to snap back when something bad happens’. The response options for all items are ordered on a five-point Likert-type scale. The scale demonstrated appropriate internal consistency, with Cronbach’s alphas ranging from 0.80–0.91 across four samples in the study (47).

The sample size calculation for the study is based on a comparison of the baseline and follow-up measures of the primary outcome, knowledge of burn-related prevention, in this cohort study. Using a previous study as a reference (22), we determined that a sample size of 478 is required to achieve a 70% improvement in knowledge of burn-related prevention, assuming a 63% rate of poor knowledge at baseline, a 5% significance level and 91.5% power at the 24-month follow-up (last follow-up). A total of 600 participants will be required, with a 20% dropout rate taken into account.

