##### Photo reflection workshops

2.3.2.2

Participants will then be invited to the photo reflection workshops. They will be asked to bring three to five of their photos for individual reflection, which will be guided by the following photo-trigger questions: Describe what you see in this Photo: How does this photo make you feel? Why did you take a photo Of this? What does this photo Tell us about your experience with burns? How can this photo provide Opportunities for us and others to improve our lives. The participants will work individually with the facilitators to produce photo captions. At the end of the workshop, the participants will be asked to fill out a questionnaire package based on the baseline measures again and will be invited to the closed local exhibitions.

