### Phase III: public dissemination of campaign messages through social media channels and community health education sessions

2.4

The priority areas for phase 3 will be determined through the findings from the photo reflection workshops and the interviews social media and health communication campaign content.

In phase 3, the participants (burn survivors) will be given instructions to continue taking photos using their mobile phones after the Photovoice workshops. They will be asked to take pictures of meaningful moments in their daily lives and reflect upon what the photos mean/represent. These instructions will also be pilot tested on a small group of individuals before being disseminated. The participants’ photos from the closed local exhibitions (based on consent) and the new photos that they capture through their mobile phones will be posted on the project website and on social media. There will be a moderation procedure in place. The research assistants will moderate online interactions by monitoring comments and responding to posts. Photos and/or stories with dedicated hashtags will be released at various high-activity times of day. Posters and/or leaflets about the social media accounts will be displayed across public spaces, such as schools and workplaces, to generate more interest in the campaign.

Health messaging will be promoted through organic and paid posts on main social media sites to increase engagement with the audience. A central website will be maintained on WordPress to host the main messages on burn prevention and first aid and will be used as a landing page for the audience to acquire more information. The website will also serve as a central repository for social media content and links for future use. The overall objective is to increase audience engagement with the campaign through likes, comments and shares.

We will run a comprehensive marketing campaign to promote the messages on Facebook, Instagram and Twitter. The promotional content will include video animations, audio/visual stories and infographics. The campaign will promote the content of the campaign and drive traffic to the project website. Broadly, we estimate to reach ~5 million people in Pakistan.

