## End of project exhibitions (nationwide)

3

Finally, we will organise a series of end-of-project exhibitions across the designated research sites in Pakistan to which a broad range of stakeholders, community workers, carers, health care professionals, policymakers and journalists will be invited. With their consent, these end-of-project exhibitions will provide a platform for the participants and others exposed to Photovoice content to talk about their experiences. We will also liaise with journalists, TV presenters, radio programmers and bloggers to disseminate the exhibitions on a national scale. Participants who took part in the Photovoice process will be asked to fill out the same questionnaire package based on the baseline measures at the end of the public exhibitions.

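### Table 1 ties the primary-outcome time points to Photovoice milestones, which conflicts with the cohort's calendar schedule and gives t1 and t2 no common meaning across groups

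*Protocol article*

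**What the plan says.** Table 1 of the Protocol article (section 2.2) has three columns: baseline (t0), Time 1 (t1) and Time 2 (t2). KAP is marked in all three, for survivors and family members. The footnote defines the follow-up points as "t1, end of photo reflection workshop; t2, end of closed exhibitions; t3, end of closed exhibition; t4, end of the final public project exhibition". The row "Campaign effectiveness^1,2,3,4" is marked at t2 only.

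Other sections time the questionnaires differently:

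- **Whole cohort, by calendar.** Section 2.1: "This study is a cohort study with three measurement points conducted at 6- to 12-month intervals". Section 2.2.3, for survivors and caregivers alike: "will be asked to complete the same questionnaires at 6- to 12-month intervals up to a total of two times throughout the study". The sample-size paragraph, at the end of section 2.2.5.10, refers to "91.5% power at the 24-month follow-up (last follow-up").
- **Photovoice participants, by event.** Section 2.3.2.2: "At the end of the workshop, the participants will be asked to fill out a questionnaire package based on the baseline measures again". Section 2.3.2.3 asks for the package again when the closed exhibitions end. Section 3 adds a further one at the public exhibitions: "Participants who took part in the Photovoice process will be asked to fill out the same questionnaire package based on the baseline measures".
- **The campaign.** Section 2.4, on what goes onto website and social media: "photos from the closed local exhibitions (based on consent) and the new photos that they capture through their mobile phones will be posted on". Section 2.3.2.3 has participants settle consent for public use of their images at the closed exhibitions.

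Section 4 fits linear mixed models with time as an interacting categorical variable, refers to Table 1 for the time points, and plans a Cohen's d for the effect of Photovoice.

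**The concern.** A categorical time factor works only if each level means the same thing for everyone. Here the table that the model cites defines its levels by events that most of the cohort does not attend, while other sections define them by calendar. Two things are at stake.

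- **Campaign effect.** The study sets out to measure short- and long-term effects of the campaign. A follow-up score taken before a participant could have been exposed says nothing about that effect, and no stated rule places t1 or t2 after launch.
- **Photovoice contrast.** If Photovoice participants are assessed as a workshop or exhibition ends and the others at 6 to 12 months, a difference at t1 mixes the effect of Photovoice with the effect of elapsed time.

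Survey timing cannot be repaired after the data are collected.

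**Working it through.** **1. Inputs.** Group sizes are 200 survivors and 100 caregivers (exposure), 250 survivors (non-exposure) and 50 survivors (Photovoice), from section 2.1. The interval is 6 to 12 months (sections 2.1 and 2.2.3). The last follow-up is at 24 months (sample-size paragraph). The study runs from March 2024 to October 2026 (section 2.1). No campaign launch date is given in the text, and Figures 1 and 2 could not be seen.

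**2. Whom the footnote can date.** Outside Photovoice: 200 + 100 + 250 = 550. Total: 550 + 50 = 600, which matches the plan. The t1 and t2 milestones describe 50 of 600 participants, or 8.3%.

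**3. Order of events under the footnote.** Section 2.4 sets the Phase III priorities from workshop findings, so t1 comes before those priorities exist. Photos must be shown at a closed exhibition, and consent for public use settled, before they are posted, so t2 precedes the public posting of those photos. The only defined point clearly after public dissemination is t4, which has no column. The t3 definition repeats t2.

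**4. The calendar schedule.** I read section 2.2.3 as two follow-ups after baseline, in line with the three measurement points in section 2.1.

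- t1: 6 to 12 months after baseline.
- t2: 2 × 6 = 12 to 2 × 12 = 24 months after baseline. The plan's 24 months is the upper end of this range.
- Study window: 10 months in 2024 + 12 in 2025 + 10 in 2026 = 32 months. Since 32 − 24 = 8, a 24-month visit fits only for people whose baseline falls in about the first 8 months.
- Let L be the months from a participant's baseline to launch (not given). A t1 visit follows launch only if L is below the actual t1 time, somewhere between 6 and 12. A t2 visit does so only if L is below the actual t2 time, somewhere between 12 and 24. The text settles neither.

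**5. Side by side.**

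| Source | Applies to | t1 | t2 or last point | Tied to launch? |
|---|---|---|---|---|
| Table 1 footnote | Photovoice events | workshop ends | closed exhibitions end | No; t2 precedes posting of those photos |
| Sections 2.1, 2.2.3 | whole cohort | 6–12 months | 12–24 months | No |
| Sample-size paragraph | whole cohort | – | 24 months | No |
| Sections 2.3.2.2, 2.3.2.3, 3 | Photovoice | workshop ends | closed exhibitions end, then public exhibitions end | Only the last follows dissemination |

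The rows do not give one date for t1 or for t2. The 24-month figure is compatible with the calendar rule. The footnote is not a definition that the whole cohort can use.

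**6. Sample size.** The inflation is 478 / 0.80 = 597.5, against the stated 600. This point does not change it.

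**The case against.** The best defence is that the calendar rule governs and the footnote is a slip. Sections 2.1 and 2.2.3 cover the whole cohort, and the sample-size paragraph names 24 months for knowledge. Milestones that the 550 do not attend could never have been meant to date their visits. Table 1 itself hints at a late t2: campaign effectiveness is marked only there, for all four participant types, and the note on the photo reflection row mentions workshops held after the public exhibitions. A five-point footnote left under a three-point table is a plausible explanation.

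Much of this stands, and it rules out several stronger readings that a reader might infer:

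- That none of the 550 has a KAP score after the campaign. The calendar sections schedule later KAP for all of them, and for the 250 non-exposed, after the campaign is only a calendar date.
- That the measured campaign effect must be null. Section 2.4 places the exhibition photos after the closed exhibitions, but does not say that animations, infographics or health education sessions wait for them.
- That the timing difference favours Photovoice. No figure supports a direction, section 2.3.1.1 calls this part a pilot, and section 4 opens with within-group comparisons.
- That Photovoice participants complete more packages than the others. The text does not say whether the event questionnaires replace or add to the calendar ones.

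What the defence does not remove is the contradiction. Even if the calendar rule governs, it is not tied to launch, it spans 12 to 24 months at t2, and it is not the definition in the table that the model cites.

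**Conclusion.** The point holds as an internal contradiction about when the primary outcome is measured. The footnote's t1 and t2 cannot date visits for 550 of 600 participants. Its t2 precedes the public posting of the closed-exhibition photos while campaign effectiveness is marked at that point. It duplicates t2 as t3 and defines a t4 without a column. It conflicts with a calendar schedule whose last visit lies 12 to 24 months after baseline and is not anchored to launch.

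Two consequences are possible but not demonstrated: the Photovoice contrast may be confounded with assessment time (direction not established), and some follow-up scores may precede exposure. How far either applies depends on the launch date and on how visits are run, which the text does not give. The conclusion rests on the printed text; an unseen figure might show the intended order, but the footnote and the calendar sections would still need to be made to agree.

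**What to change.** - Define t1 and t2 once, identically for all three groups, by elapsed time with a fixed window. State that t2, and with it campaign effectiveness, falls after campaign launch.
- Keep the questionnaires at the end of the workshops, closed exhibitions and public exhibitions as process measures outside the t1/t2 comparison. Say whether they are additional to the scheduled visits.
- Delete t3 and t4 from the footnote, or give them columns.
- Reconcile section 2.1, Table 1 and its footnote, section 2.2.3, the sample-size paragraph, sections 2.3.2.2, 2.3.2.3 and 3, and the time points in section 4, so that all refer to the same t1 and t2.

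The cost is a corrected table, edits to the procedure text and a revised survey calendar. The sample size does not change. Some survey dates may move later, and whether they still fit before the end of October 2026 needs checking against the launch date.

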#### Sampling

2.2.1

A combination of snowball and purposive sampling methods will be used to identify and recruit patients (burn survivors), caregivers and key stakeholders (i.e., health and emergency care professionals and key informants, including community leaders and policymakers), based on the eligibility criteria described below.

#### Participants

2.2.2

A wide range of participants will be recruited for the study. As the media interventions vary in scope and objectives, not all participants will receive the same questionnaires and Photovoice intervention. Below, we describe the scales to be administered to each participant.

#### Procedure

2.2.3

The research team will recruit burn survivors and caregivers from 12 burn centres based in seven project sites across Pakistan to measure existing indicators of knowledge, attitudes and practices on burn prevention, as well as psychological variables, health information-seeking variables and demographics.

Burn survivors and their family members will be invited to fill out online questionnaires (baseline assessment). The research assistants will distribute posters and leaflets at participating centres and waiting rooms, introducing the study and providing the research team’s contact information for further enquiries. The research assistants will also attend the patient and/or family consultations to introduce the study and obtain consent for a follow-up call with the research team. During the follow-up call (within the first 24 or 48 h after the initial contact), the research assistants will ensure that interested burn survivors and their family members understand what their participation entails, and will confirm their willingness to provide informed consent. After informed consent is obtained, burn survivors and their family members will be asked to complete the same questionnaires at 6- to 12-month intervals up to a total of two times throughout the study (see Figure 2 for the CONSORT diagram). If they are literate, as determined during the informed consent process, they will receive a text message with a Qualtrics questionnaire link. If they are illiterate, a research assistant from the research team will call them for the completion of the questionnaires on the phone. Consent for collecting personal information will be obtained during the informed consent process.

**Figure 2 fig2:**
[figure not shown]
CONSORT diagram.

The rest of the participant groups, including key stakeholders (i.e., health and emergency care professionals) and key informants (i.e., community leaders and policymakers), will be recruited purposively for the development and implementation of the social media and health communication campaign (see Figure 1 for the project activities). They will provide input on the content of the campaign messages, dissemination and campaign reach.

#### Eligibility criteria

2.2.4

##### Burn survivors

2.2.4.1

The following are the inclusion criteria for burn survivors:

Adults aged 18 years and aboveRecent (i.e., within the past 3 months) and/or past experience of a burn injuryResides in one of the seven research sitesAble to provide consent and participate in the mixed methods study, which requires their engagement in project activities, including surveys, Photovoice reflection workshops and closed/open exhibitions depending on the group to which they are assignedFor those involved in the Photovoice group, an additional criterion includes willingness to engage with participatory creative methods, such as photography and storytelling, as well as availability to attend a minimum number of Photovoice workshops.

The following are the exclusion criteria:

Burn survivors with intentional and/or self-inflicted injuries will be signposted to the available services for further help and will not be included in the study.

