**Methods and analysis:**

This cohort study will follow 600 participants (*n* = 600; *n* = 500 burn survivors; *n* = 100 caregivers) with three measurement points at 6- to 12-month intervals. The primary outcomes are knowledge, attitudes and practices regarding burn injuries. The secondary outcomes are meaning in life; gratitude, resentment and appreciation; hope; optimism; temporal satisfaction with life; coping strategies; social interaction anxiety; self-stigma and resilience, measured using the Meaning in Life Questionnaire, the Gratitude, Resentment and Appreciation Scale, the Adult Workers Hope Scale, the Patient Optimism Scale, the Temporal Satisfaction with Life Scale, the COPE Inventory, the Social Interaction Anxiety Scale, the Self-Stigma Scale and the Brief Resiliency Scale, respectively. The participants are grouped as follows: the exposure group (i.e., burn survivors [*n* = 200] and caregivers [*n* = 100] exposed to campaign messages), the non-exposure group (i.e., burn survivors [*n* = 250] not exposed to campaign messages) and the Photovoice group (i.e., burn survivors [*n* = 50] who participate in Photovoice and are exposed to the campaign messages). This design evaluates the impact of the health communication campaign and determines whether Photovoice has any additional effects on the primary and secondary outcomes.

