##### Sampling

2.3.1.1

To investigate the preliminary effects of Photovoice on the primary and secondary outcomes of interest, we will categorise participants into three groups, as described previously (see Figure 1). As this is only a pilot study and the objective is mostly to co-adapt the Photovoice programme and evaluate its potential in building capacity for a larger evaluation, no sample size calculation has been deemed appropriate (48, 49). This study will also help us determine whether we can maintain an acceptable attrition rate of Photovoice for a future RCT (50). An effective sample size for this study was determined based on the sample size of previous exploratory studies using Photovoice (31).

Consenting baseline participants will be invited to attend the introductory Photovoice workshop via email and/or a telephone call. The invitation letters will be sent via email and/or postal mail. One-to-one meetings will be organised with those who do not want to be in a group setting.

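### Only the Photovoice group must be willing and available, and no allocation rule is given, so the Photovoice contrast mixes any effect with volunteer traits

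*Protocol article*

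**What the plan says.** The Abstract and section 2.1 (Research design) describe a cohort in three groups. The exposure group is "burn survivors [*n* = 200] and caregivers [*n* = 100] exposed to campaign messages", the non-exposure group is 250 burn survivors, and the Photovoice group is "burn survivors [*n* = 50] who participate in Photovoice and are exposed to the campaign messages".

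Section 2.2.4.1 (Burn survivors) adds an entry condition for the Photovoice group only: "an additional criterion includes willingness to engage with participatory creative methods, such as photography and storytelling". A second condition for that group, in the same sentence, concerns their time: "as well as availability to attend a minimum number of Photovoice workshops". The same section speaks of the group a participant is assigned to, without saying how assignment is made.

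Section 2.3.1.1 (Sampling, under Photovoice) says "we will categorise participants into three groups, as described previously" and then: "Consenting baseline participants will be invited to attend the introductory Photovoice workshop via email and/or a telephone call". Section 2.2.1 gives the recruitment method as snowball and purposive sampling.

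On what the comparison is for, the Abstract says the design "determines whether Photovoice has any additional effects on the primary and secondary outcomes". The objectives at the end of the Introduction, and section 2.3.1.1, are more modest. They call the effects preliminary, describe this part as a pilot and look ahead to a future randomised trial.

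Section 4 (Data analysis plan) defines Cohen's *d* for Photovoice from baseline-corrected means, with a two-sided 5% threshold. Demographics enter the models to test moderation and mediation of behavioural intention, and stepwise AIC decides which variables stay.

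**The concern.** To isolate what Photovoice adds to the campaign, the two groups should differ only in Photovoice. Here they also differ in entry criteria. Everyone in the Photovoice group is ready to photograph and tell their story and has time for workshops; among the exposed survivors some would be and some would not. That readiness plausibly relates to the outcomes under test, such as self-stigma, social interaction anxiety, hope and resilience, and to how far a person takes up health messages.

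If volunteers would have improved more than others under the campaign alone, the planned *d* credits that improvement to Photovoice. If they would have improved less, a real benefit could be hidden. This is bias, so a larger sample would not cure it, and an inflated *d* could mislead the planning of the later trial. A later analysis plan cannot adjust for answers never collected from the comparator. Neither section 2.2.5 (Measures) nor Table 1 names willingness or availability.

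**Working it through.** **The plan's own figure.** None exists for this comparison; section 2.3.1.1 says no sample size calculation was deemed appropriate. The whole-cohort figure (478, raised to 600) concerns a before-after change in knowledge and does not bear on this point. The group sizes are consistent: 200 + 100 + 250 + 50 = 600.

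**Does the planned analysis remove the selection?**
- Baseline-corrected means deal with stable differences in starting level. Survivors complete all the psychological scales at baseline (Table 1), so this part is covered.
- They do not deal with a difference in change that would have occurred without Photovoice.
- Demographics could absorb some of that difference, but they are entered for another purpose and a confounder can be dropped by AIC.
- No step in section 4 addresses willingness or availability.

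**Inputs for an illustration.**
- Group sizes 50 and 200 survivors (section 2.1). Caregivers are left out because Photovoice participants are all survivors; the article does not name the comparator explicitly.
- Two-sided 5% (section 4) and 20% dropout (end of section 2.2.5).
- Assumed: true Photovoice effect zero; equal SDs; a residual volunteer difference in change of *b* SD, taken as 0.1, 0.2 and 0.3. The documents give no value for *b*.

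**Formulas.** SE = √(1/n₁ + 1/n₂), in SD units. Chance of a significant result = Φ(b/SE − 1.96) + Φ(−b/SE − 1.96).

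**Standard errors.**
- No dropout: √(1/50 + 1/200) = √0.025 = 0.158.
- 20% dropout in both groups (40 and 160): √(1/40 + 1/160) = √0.03125 = 0.177.

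| *b* (SD) | 50 v 200 | 40 v 160 |
|---|---|---|
| 0 | 5% | 5% |
| 0.1 | 9.7% | 8.7% |
| 0.2 | 24.4% | 20.5% |
| 0.3 | 47.5% | 39.6% |

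Example for *b* = 0.2 without dropout: b/SE = 0.2/0.158 = 1.265; Φ(−0.695) + Φ(−3.225) = 0.244.

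**Precision cost of a willing-only comparator.** If 100 of the 200 exposed survivors meet both criteria (an assumption), SE = √(1/50 + 1/100) = √0.03 = 0.173 instead of 0.158. The difference detectable with 80% power is (1.960 + 0.842) × SE, which goes from 0.44 to 0.49 SD.

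**The case against.** The strongest reply is that the article does not oversell this part. It is a declared cohort, it claims no randomisation, and both the objectives and section 2.3.1.1 treat the Photovoice effects as preliminary and the work as a pilot. Willingness is also intrinsic to consenting to photography and storytelling. This stands as far as severity goes. It does not make the contrast interpretable, and the Abstract's claim carries no such limit.

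A second reply is that the traits most likely to differ are measured at baseline and corrected for. That is right for starting level and is a real strength of the plan. It leaves differential change.

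A third is that the error rates rest on assumed volunteer differences. That is also right: they show what bias of a given size would do, not that it is present.

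A reader might go further and infer that every consenting participant is invited, including the 250 non-exposed survivors, so that the Photovoice group is simply whoever accepts and the exposure group holds those who declined. The text does not support this. Section 2.3.1.1 does not say that all are invited, it speaks of categorising participants, and section 2.2.4.1 speaks of assignment. Investigators may therefore set the groups before any invitation goes out. Figures 1 and 2, which might show the order, are not available here. The difference in entry criteria holds under either reading.

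**Conclusion.** The point holds in limited form. As written, the Photovoice group passes a willingness and availability filter that its comparator does not, no allocation rule is stated, and the planned analysis does not control for that filter. The contrast of 50 with 200 survivors cannot separate taking part from being the kind of survivor who takes part, so the Abstract promises more than the design can deliver.

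The size of the bias is unknown. Over the assumed range of 0.1 to 0.3 SD, the false-positive rate would be roughly two to nine times the nominal 5%. Given the pilot status, this is a cheap and worthwhile improvement to an exploratory comparison. It does not undermine the cohort as a whole.

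**What to change.** 1. Ask the willingness and availability questions of all 500 survivors at baseline, before groups are set.
2. Make the primary Photovoice comparison against exposure-group survivors who also met both criteria. Adjust for the baseline outcome and a fixed set of demographics that stepwise selection cannot remove.
3. State in section 2.3.1.1 which group the workshop invitation goes to, and when groups are set relative to it.
4. Reword the Abstract to say that the design explores preliminary additional effects of Photovoice, in line with the objectives and section 2.3.1.1.

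Comparing willing with willing reduces the bias but does not remove it, because how the 50 are chosen among the willing still matters. Where willing survivors outnumber places, a stronger option is to draw the 50 by lottery at each centre and use undrawn willing exposure-group survivors as the comparator. That is a larger design change. It also needs a stated rule for dividing undrawn willing survivors between the exposure and non-exposure groups.

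Cost of items 1 to 4: two extra questions, edits to the text and a smaller comparator (SE about 0.17 instead of 0.16 SD if half are willing). No extra participants, visits or staff are needed. The answers must be collected before groups form, so item 1 cannot be recovered later.
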